**HYPOTHESIS**

Number of EMB performed in the first year post-HT could vary depending on IMR values. Low IMR values in the first three months could reduce the number of protocol EMB. Meanwhile, high IMR values would not modify the number of EMB performed, and could even contribute to intensify immunosuppressive therapy.

**METHODS**

This is a multi-center, prospective, observational study of HT patients at the participating centers. The recruitment period of the study is two years.

*Informed consent:* All the patients will sign informed consent specifically designed for this study.

***Inclusion criteria***

- Heart transplant patients >18 years.
- Patients who have received and signed informed consent.

***Exclusion criteria***

- Patients with hemodynamic instability after HT, including cardiogenic shock or severe coagulopathy.
- Patients with acute cellular rejection before intracoronary physiological assessment.
- Patients with bronchial asthma or bronchopathy with a positive bronchodilation test, which contraindicates the use of adenosine.
- Patients with epicardial coronary lesions with a resting physiological index ≤0.89 or ≤0.80 at hyperemia.
- Patients unlikely to cooperate or with inability or unwillingness to give informed consent.

***Procedure***

**Invasive physiological evaluation of the coronary microcirculation**

Patients included will undergo a coronary angiography between the first and third month after HT.  This coronary angiography is part of the follow-up protocol in most of the centers. Assessment of IMR, coronary flow reserve (CFR) and fractional flow reserve (FFR) will be performed using the standard technique (9-10,14).

The left anterior descending coronary artery will be evaluated in all patients. Circumflex or right coronary artery could be additionally evaluated at operator’s discretion. An intracoronary pressure and temperature sensor-tipped guidewire (Pressure Wire TM X guide- wire 0.014’, Abbott, IL, USA) will be used to perform the measurements. The tip pressure sensor will be advanced into the mid-to-distal portion of the evaluated vessel. Baseline aortic pressure (Pa) and distal intracoronary pressure (Pd) will be obtained to calculate the resting index Pd/Pa. To measure the mean transit time (Tmn) under basal conditions, intracoronary administration of 3 mL of room-temperature saline will be manually injected three times in succession (3 mL/s). Then maximal hyperemia will be induced using adenosine iv (140 to 180 mg/kg/min) and three additional intracoronary room temperature saline boluses of 3 ml will be administered to determine the mean transit time at hyperemia (Tmnh). Finally, fractional flow reserve (FFR), coronary flow reserve (CFR) and IMR will be calculated using the software Coroventis Coroflow (*Coroventis Abbott, Uppsala, Sweden)*.

- FFR is defined as the ratio of maximal coronary blood flow in a diseased artery to maximal coronary blood flow in the same artery without stenosis. FFR is a surrogate marker of inducible myocardial ischemia caused by epicardial coronary stenosis.

- CFR is the ratio of hyperemic to baseline flow and is a marker of the integrity of both epicardial and microvascular coronary circulation. Therefore, CFR represents the microvascular status when there is no significant epicardial disease.

- IMR is the minimum achievable coronary microcirculatory resistance and a more specific marker of the coronary microcirculation. It is calculated as the ratio of distal coronary pressure to coronary flow at hyperemia and presented in units (mmHg.s).

The physiological study assessing IMR, CFR and FFR will be repeated again one year after HT.

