## 3.6. Sample size

## 3.7. Recruitment

In 2023, around 325 heart transplants (HT) were performed in Spain Given a median of 10-15 HT per center and considering that eight centers that routinely perform invasive coronary physiology are participating, data will be analyzed when 100 patients have completed first year follow-up.

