***Definition of principal variables***

- **Pa:** basal proximal (aortic) pressure.
- **Pah:** aortic pressure at maximal hyperemia.
- **Pd:** basal distal pressure.
- **Pdh:** distal pressure at maximal hyperemia.
- **Tmnr:** Mean transit time of the saline injected at rest.
- **Tmnh:** Mean transit time of the saline injected at maximal hyperemia.
- **RFR:** Resting index calculated on the basis of the lowest Pd/Pa value throughout the cardiac cycle. A value ≤0.89 is associated with functionally significant coronary stenosis.
- **FFR:** Hyperemic index calculated by Pdh/Pah quotient. FFR ≤0.80 is associated with functionally significant coronary stenosis.
- **CFR (coronary flow reserve):** This parameter explores the maximal vasodilation capacity of the entire coronary bed (epicardial and microvascular), and hence the increase in coronary flow compared with the resting value.

The fundamental principle is the inversely proportional relationship between the coronary flow and transit time (TT) of a bolus of intracoronary saline, estimated on the basis of the change in temperature. CFR is considered to be low when is <2; normal >2.5.

CFR= 1/(Tmnh/Tmnr)

- **IMR (index of microcirculatory resistance):** This index reflects microvascular function regardless of epicardial circulation. It is obtained in a state of maximal hyperemia. A value ≥25 is considered pathological; normal <20. In our study, an IMR ≥15 will be considered high (8).

IMR= Pdh x Tmnh.

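### The only adenosine rate in the protocol is printed in mg/kg/min, which means grams per minute in an adult; the mass unit appears wrong and needs checking

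*Protocol*

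**What the plan says.** The dose stands in the Protocol, under Procedure, *Invasive physiological evaluation of the coronary microcirculation*: "Then maximal hyperemia will be induced using adenosine iv (140 to 180 mg/kg/min". The same section says of the measurements of IMR, CFR and FFR that they "will be performed using the standard technique (9-10,14", that is, by citation of references 9, 10 and 14.

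Adenosine is otherwise mentioned only as a contraindication. The exclusion criteria, given in section 3.2, in the summary table under section 5.3.1 and again in the Methods text, list: "Patients with bronchial asthma or bronchopathy with a positive bronchodilation test, which contraindicates the use of adenosine". None of these places gives a dose, a maximum rate, a concentration or an infusion time.

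The step matters to the study because of how IMR is defined. Under *Definition of principal variables* the protocol says of it: "It is obtained in a state of maximal hyperemia". The functional study is done between the first and third month after transplant and repeated at one year.

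**The concern.** A weight-based rate in milligrams per kilogram per minute, at a value of 140 to 180, implies grams of drug per minute into a vein. That is implausible on its face, without any outside source. The line is current procedure text in a multicenter protocol, and a site could copy it into a worksheet or an infusion order.

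If the source file really prints mg, following the instruction exactly would be dangerous. Each patient has two planned studies, so a target of 100 patients implies up to 100 × 2 = 200 infusions. The protocol offers no second figure that would expose the error. Section 3.14 (Safety/harms) is marked not applicable. Catheterization complications are defined as an event, but that records harm after the fact and does not check a dose.

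**Working it through.** **Inputs**

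- Rate as printed: 140 to 180 mg/kg/min (Procedure, invasive physiological evaluation).
- Population: "Heart transplant patients >18 years" (Inclusion criteria). No body weight is given, so 50, 70 and 100 kg are assumed here.
- Intended mass unit: not given anywhere. Micrograms is taken as the alternative, as an assumption.

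The protocol gives no calculation behind the rate, so there is no derivation to reproduce. The check is unit arithmetic only.

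**Formula:** rate (mg/kg/min) × weight (kg) ÷ 1,000 = g/min.

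| Assumed weight | Lower end | Upper end | As printed (mg) | If micrograms were meant |
| --- | --- | --- | --- | --- |
| 50 kg | 140 × 50 = 7,000 mg/min | 180 × 50 = 9,000 mg/min | 7.0 to 9.0 g/min | 7.0 to 9.0 mg/min |
| 70 kg | 140 × 70 = 9,800 mg/min | 180 × 70 = 12,600 mg/min | 9.8 to 12.6 g/min | 9.8 to 12.6 mg/min |
| 100 kg | 140 × 100 = 14,000 mg/min | 180 × 100 = 18,000 mg/min | 14.0 to 18.0 g/min | 14.0 to 18.0 mg/min |

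The last column is the printed figure divided by 1,000.

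**Accumulated dose.** An assumed infusion of two minutes, as printed, would deliver 2 × 7.0 = 14 g at the lowest combination and 2 × 18.0 = 36 g at the highest.

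**Does the choice of weights matter?** No. One kilogram is 1,000,000 mg, so 140 mg/kg is 140 ÷ 1,000,000 = 0.014% of body mass and 180 mg/kg is 0.018%, every minute, whatever the patient weighs.

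**Is the unit corrected elsewhere?** No. Every other mention of adenosine is the asthma and bronchopathy exclusion, without a dose.

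**The case against.** The strongest objection is that the point turns on one letter, and the text at hand was extracted from a file by a program. If the source set the micro sign as a letter in a symbol font, extraction could return m, and the protocol would then contain no error. Other special characters did survive: the ≥ and ≤ signs in several sections, ± in section 3.12.1 and the middle dot in the IMR unit in section 3.4. That leans weakly towards mg being in the source. It is not proof, since those may be ordinary characters and no micro sign appears anywhere to serve as a test. This objection stands as a reason for medium confidence and for checking the source first. It is not a reason to leave the line alone.

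The second objection is that nobody would act on the figure. The measurement is tied to a cited standard technique, and section 3.7 says that "eight centers that routinely perform invasive coronary physiology are participating". A rate of several grams per minute is conspicuous, and experienced operators would probably disregard it. This also stands, and it limits the practical risk. It does not make the printed rate right.

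Third, the step from an implausible unit to a factor of 1,000 depends on micrograms being meant, which the protocol does not say. That is correct, and the factor is offered only on that assumption. The narrower statement, that the rate is unusable as printed, needs no such assumption.

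Finally, this is a unit slip and not a failed calculation in the plan. That is a fair description, but it does not change what has to be done.

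**Conclusion.** The point holds with medium confidence. As printed, the protocol's only adenosine rate cannot be used in an adult, and no other text repairs it. The g/min figures rest on the assumed weights; the conclusion does not. The remaining uncertainty is whether the source file prints mg or a micro sign.

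The consequence is confined to dosing safety. No effect on sample size, power, significance level, endpoints or the statistical methods follows from it, and nothing in the protocol shows that the measured IMR or the classification at 15 would change. It should be fixed because a dose in operative procedure text ought to be correct even where experienced staff would catch the error.

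**What to change.** 1. Open the source file and read the unit in the adenosine sentence. If it is a microgram unit, the matter is closed and nothing changes.
2. If it is mg, correct the unit against references 9, 10 and 14 and the product label. Writing the mass unit out in words would prevent a later misreading of the symbol.
3. In that case, send the participating centers a short notice of the correction and ask them to check any local worksheet or order set that was copied from the protocol.

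The cost is one look at a file and, if the error is confirmed, a one-line correction with a site notice. Design, endpoints and analysis are untouched.

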***Biopsies and immunosuppressive therapy***

Based on IMR results:

- If the IMR is less than 15, the number of biopsies could be reduced or kept the same. No immunosuppressive therapy changes would be made.

- If the IMR is 15 or greater, immunosuppressive therapy could be intensified or maintained the same. Number of biopsies would be performed as usual per protocol.

Given the observational characteristics of the study, decisions regarding clinical patient management will depend on physician discretion considering patient clinical condition and other complementary tests.

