## 3.12. Statistical methods

### 3.12.1. Outcomes

The characteristics of the study population will be summarized through standard descriptive statistics. Continuous variables will be expressed as mean (± standard deviation) or median [interquartile range (IQR)], as appropriate. Discrete variables will be presented as absolute numbers and percentages. For the comparison of means, the Student's t test for independent measures or the non-parametric Mann-Whitney U test (in the case of dichotomous qualitative variables) and the ANOVA or non-parametric Kruskal test will be used as a hypothesis test. Wallis (in the case of non-dichotomous qualitative variables). For the bivariate analysis of the qualitative variables, the Chi-square test or Fisher's exact test will be used. Events will be compared between groups by using Kaplan-Meier curves. Cox regression analysis will be performed to adjust for confounding factors and to evaluate independent predictors of clinical events. A two-tailed p-value of 0.05 will be considered statistically significant. All statistical analyses will be performed by SPSS software version 20.

In 2023, around 325 heart transplants were performed in Spain (3). Given a median of 10-15 HT per center and considering that eight centers that routinely perform invasive coronary physiology are participating, data will be analyzed when 100 patients have completed first year follow-up.

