**INTRODUCTION AND RATIONALE**

Heart transplant (HT) is considered the treatment of choice for patients with advanced heart failure refractory to medical treatment or devices.

Acute allograft rejection (AAR) is the main cause of mortality and re-transplantation,  particularly during the first year. The immune response is classified into acute cellular rejection (ACR) when mediated by T lymphocytes, and humoral rejection when involving B lymphocytes and antibody production. Of note, up to 20% of HT patients experience at least one episode of ACR during the first year post-transplantation (1). Advances in immunosuppressive therapy (IST), donor heart evaluation, surgical techniques and post-HT care have led to a reduction in ACR, improving survival over time (2-3). Post-transplant IST includes three basic components: a calcineurin inhibitor (currently preferred Tacrolimus), an antiproliferative agent (mycophenolate mofetil), and steroids. On the other hand, proliferation signal inhibitor (mTOR) drugs (everolimus and sirolimus) are primarily used for CAV (3-4). CAV is the main cause of mortality after the first year of transplantation. It is characterized by diffuse intimal thickening affecting both coronary epicardial and microcirculation (2,4).

The vast majority of ACR occur asymptomatically with normal ventricular function, and thus being detected by endomyocardial biopsy (EMB). EBM is the "gold standard" to guide post-HT treatment (4). The graduation of the RAC is detailed in the 2005 review of the ISHLT (5). Due to intra- and inter-observer variabilities in determining different degrees of slight-moderate rejection, an update was published in the 2010 document. In the International Society of Heart and Lung Transplantation (ISHLT) guidelines, EMB was made a IIaC recommendation for the detection of rejection (2). EMB is repeatedly performed during the first year after HT and is associated with complications that, despite infrequent, can be potentially serious, such is the case of cardiac perforation. Moreover, EMB diagnostic yield is wide, with a high variability between observers and a non-negligible rate of false positives and negatives (6).

In order to avoid the inconveniences of EMB, non-invasive techniques have been studied to detect rejection, with some positive results. However, none of these techniques has been able to replace EMB (7).

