Various studies have demonstrated the association between ACR, microvascular dysfunction (MVD) and cardiac allograft vasculopathy (CAV) (8). IMR is a quantitative and specific index for coronary microcirculation (9-10).  An increased IMR in the graft has been associated with higher all-cause mortality and adverse cardiac events regardless of epicardial vasculopathy (11). Several IMR cut-off (from 15 to >25) have been associated with ACR within the first year after HT. Patients in whom IMR decreases or does not change one year after HT have a higher event-free rate than those patients in whom the IMR increases (12-13). However, no study has evaluated IMR impact on post-HT management. In presence of a low IMR value, EMB could be performed less frequently; on the contrary, if the IMR value is high, immunosuppression therapy could be modified by an earlier administration of mTor-inhibiting drugs or prescribing calcium antagonists, which are known to improve microvascular function.

Our aim will be to assess if post-HT patient management may be safely modified based on IMR value.

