**STUDY DESIGN**

**ENDPOINTS**

*The main objective* of the study is to evaluate IMR values and number of EMB performed in the first year after HT.

S*econdary endpoints* are:

- Analyze the relationship between ACR and IMR.
- Analyze the relationship between CV mortality and IMR.
- Analyze the relationship between CAV and IMR.
- Analyze the relationship between the variation IMR value in the first two months and one year, and cardiovascular events.
- Analyze the relationship between the combined endpoint of ACR, heart failure, re-transplantation, CV mortality and IMR.
- Assessment of immunosuppressive therapy after IMR results.

All endpoints will be evaluated at 1 year, and annually thereafter for up to 5 years.

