***Definition of events***

- **Acute cellular rejection (ACR**): A ≥2R degree according to the 2010 ISHLT system. Two or more focal infiltration points associated with myocyte injury in EMB. Diffuse infiltration with multi-focal myocyte injury with/without oedema, hemorrhage or vasculitis (2).
- **Cardiovascular mortality:** Caused by cardiovascular disease or unknown death.
- **Cardiac allograft vasculopathy:** Accelerated fibroproliferative process characterized by diffuse, concentric and longitudinal thickening of the intima of the vascular tree of the graft, affecting everything from the major epicardial arteries to the coronary microvasculature (2).
- **Combined endpoint:** ACR, heart failure, re-transplantation and cardiovascular mortality.
- **Cardiac catheterization complications:** any complication (major or minor) related to the performance of EMB, coronary angiography and functional study.

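### Recorded rejection by IMR group mixes rejection risk with biopsy frequency, because a low IMR permits fewer biopsies and biopsy is how most rejection is detected

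*Protocol*

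**What the plan says.** The protocol's section *Biopsies and immunosuppressive therapy* sets a different rule on each side of the IMR cut-off. Below 15: "If the IMR is less than 15, the number of biopsies could be reduced or kept the same". At 15 or above: "Number of biopsies would be performed as usual per protocol", and immunosuppression may be stepped up. Both are left to the physician's judgement. Sections 3.3.1 and 3.4 repeat the biopsy rule, and the hypothesis is that low IMR leads to fewer biopsies.

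ACR is defined by histology (*Definition of events*): "A ≥2R degree according to the 2010 ISHLT system". On how it comes to light, *Introduction and rationale* says: "The vast majority of ACR occur asymptomatically with normal ventricular function, and thus being detected by endomyocardial biopsy (EMB").

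A secondary endpoint (*Endpoints*) is: "Analyze the relationship between ACR and IMR". The combined endpoint also contains ACR: "ACR, heart failure, re-transplantation and cardiovascular mortality". Section 3.12.1 gives the analysis: "Events will be compared between groups by using Kaplan-Meier curves", with Cox regression for confounders that are not named. The introduction gives the wider purpose: "Our aim will be to assess if post-HT patient management may be safely modified based on IMR value".

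**The concern.** The exposure influences how often the outcome is looked for. An ACR event needs a biopsy, most episodes give no other signal, and one exposure group may be biopsied less because of its exposure. The protocol sets no biopsy time point common to both groups, does not separate surveillance from for-cause biopsies, and does not bring biopsy frequency into the analysis.

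Two readings of the result are at stake: that IMR predicts rejection, and that reducing biopsies at low IMR was safe. Missed rejection would lend support to both, and more so the further biopsies are cut. The composite inherits the problem through its ACR component.

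**Working it through.** The protocol gives no figure to reproduce here. The direction follows from its text. The size needs assumptions.

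**From the protocol:** up to 5 biopsies in year one (section 2.1); IMR measured between months 1 and 3 (*Procedure*); up to 20% of patients with ACR in year one (introduction); analysis at 100 patients (section 3.7). The number of biopsies in low-IMR patients is left to each centre.

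**Assumed, not in the protocol:** equal true risk in both groups; constant hazard with 15% onset between weeks 8 and 52; usual biopsies after IMR at weeks 16, 24, 36 and 52; an episode detectable for w = 4 to 8 weeks; a share s = 10% to 20% symptomatic and found anyway.

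**Formulas**
- Hazard: λ = −ln(0.85)/44 = 0.00369 per week.
- Chance that onset falls in weeks a to b: exp(−λ(a−8)) − exp(−λ(b−8)).
- C = sum of that chance over the w weeks before each biopsy.
- Detected proportion = 0.15s + (1−s)C.

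**Example** (w = 8, s = 0.10). Four biopsies: C = 0.1099, detected = 0.015 + 0.9 × 0.1099 = 11.39%. Two biopsies (weeks 24, 52): C = 0.0538, detected = 0.015 + 0.9 × 0.0538 = 6.34%. Ratio 11.39/6.34 = 1.80, where the truth is 1.0.

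The two rows below are the extremes over w = 4, 6, 8 and s = 10%, 20%. Each cell gives the percentage detected in the low-IMR group, with the high/low ratio in brackets.

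| Inputs | None cut | Week 36 dropped | Half of patients at 2 | All at 2 | All at 1 (week 52) |
|---|---|---|---|---|---|
| w = 4, s = 20% | 7.36 (1.00) | 6.29 (1.17) | 6.25 (1.18) | 5.13 (1.43) | 4.01 (1.84) |
| w = 8, s = 10% | 11.39 (1.00) | 8.96 (1.27) | 8.87 (1.28) | 6.34 (1.80) | 3.79 (3.00) |

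**Second model, as a cross-check.** Take a constant yield p per biopsy such that five biopsies detect 20%: 1 − (1−p)^5 = 0.20, so p = 0.0436. Then 4, 3 and 2 biopsies detect 16.4%, 12.5% and 8.5%, giving ratios of 1.22, 1.60 and 2.34. With 100 patients split evenly, the chance of a spurious significant finding that high IMR carries more ACR is about 7%, 17% and 37%, against 2.5% in that direction without the bias. This model treats all five biopsies as open to change and every episode as silent, so it leans high. If only half of low-IMR patients are cut, to 3 or to 2, its ratios fall to 1.23 and 1.40.

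**The opposing influence.** If intensified immunosuppression lowers true risk at IMR ≥15, the detection effect shrinks or reverses. In the first model the all-halved case is cancelled by a true reduction of 1 − 1/1.43 = 30% to 1 − 1/1.80 = 44%.

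**Does a per-biopsy analysis help?** In the example, the yield per surveillance biopsy is proportional to 0.1099/4 = 0.0275 against 0.0538/2 = 0.0269, a ratio of 1.02. The artefact almost disappears.

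**The case against.** A reader might infer that the comparison must flatter IMR, or that a two- or three-fold artefact is to be expected. The protocol supports neither. Biopsies at low IMR may be reduced or left alone, at the physician's discretion, and if none are cut the ratio is 1.0. The upper figures need every low-IMR patient to be cut to two biopsies or one. IMR may be measured as late as month 3, so fewer than four biopsies may remain to be changed. Possible intensified treatment at high IMR leaves the net direction open. Nor does the protocol say that ACR is found only by biopsy; it says the vast majority of episodes are silent. All of this stands and limits the claim.

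It is also true that the primary outcome is untouched, that ACR by IMR is a secondary endpoint, and that heart failure and mortality, which do not depend on biopsy, are already listed.

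Two further defences are weaker. One is that a statistical analysis plan may settle the model. It may, but the protocol itself names Kaplan-Meier and Cox, and the reason for each biopsy has to be recorded as data before any plan can use it. The other is that Cox will adjust for confounders. Biopsy count is set after IMR and rises when rejection is suspected, so entering it as a covariate would not repair the comparison. Finally, two opposing biases of unknown size do not make the result interpretable.

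**Conclusion.** The concern holds in a limited form. As planned, the comparison of ACR and of the composite by IMR group does not separate rejection risk from detection intensity. With equal true risk, any real reduction in biopsies lowers recorded ACR at IMR <15. The detected risk ratio runs from 1.0 (no reduction), through about 1.2-1.3 (one biopsy dropped, or half of low-IMR patients halved) and 1.4-1.8 (all halved), to 1.8-3.0 (all cut to one). These sizes rest on the assumed onset rate, biopsy timing, detectable window and symptomatic share; the equal-risk direction does not. The net direction in the actual data cannot be stated in advance. The number of biopsies as primary outcome is not affected, but a claim that management was safely modified cannot rest on this ACR comparison.

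**What to change.** 1. Analyse ≥2R per surveillance biopsy performed, with only surveillance biopsies in numerator and denominator: a patient-clustered GEE, or Poisson with the log number of surveillance biopsies as offset. Alternatively, treat ACR as interval-censored between biopsies, which assumes that an episode is still visible at the next one. Either replaces plain Kaplan-Meier and Cox on first detected ACR.
2. Record each biopsy in REDCap as surveillance or for-cause, and back-fill patients already enrolled.
3. Show the composite with and without surveillance-detected ACR.
4. Rest any safety statement on outcomes already named and not found by biopsy (heart failure, re-transplantation, cardiovascular and all-cause death), comparing all patients with IMR <15 against all with IMR ≥15. Do not use only those whose biopsies were reduced, since physicians select them and they have no comparator. Treat for-cause ≥2R as supportive only: surveillance that catches an episode early removes a later for-cause event.
5. Describe the estimate as the association under IMR-guided care, and do not adjust for immunosuppression changed after IMR.

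The cost is some wording, one database field and back-filling at centres that have been enrolling since March 2024. The outcomes not found by biopsy will have fewer events and wider intervals. No change to any biopsy schedule or treatment is proposed.
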